## Abstract

**Background:**

Although largely preventable through diet management and topical fluoride use, early childhood caries (ECC) often progresses to severity that necessitates surgical repair. Yet repair often fails to mitigate caries progression. Needed is an effective behavioral intervention to address underlying behavioral causes.

**Methods:**

This randomized controlled trial will evaluate the efficacy of a behaviorally focused, family-centered intervention, the MySmileBuddy Program (MSB Program), to reduce ECC progression in high-risk preschoolers in New York City. Recruitment will target 858 children ages 24–71 months with ECC and their parents from primary care medical and dental clinics. The study aims to assess the MSB Program’s efficacy to: (1) decrease ECC progression measured 12-months post-randomization; and (2) enhance adoption of a low cariogenic diet and twice-daily fluoridated toothpaste use compared to control group. Potential causal pathways (mediators and moderators) will be explored. The MSB Program equips community health workers (CHWs) with an app that facilitates multilevel risk assessment and provides motivational interviewing-based counseling to inform parents about the caries process, develop personalized goals, and create family-level action plans to achieve targeted behaviors. Social support from CHWs (4 interactions during the 6-month intervention, supplemented by up to 4 in-person/remote contacts throughout the 12-month study period, based on need) is bolstered by automated text messages. Participants will be randomized to a Control Group (paper-based educational handout plus toothbrushes and fluoridated toothpaste for the child) or Intervention Group (MSB Program, two tooth-brushing observations with feedback and instruction, and toothbrushes and toothpaste for the entire family). All children will receive visual ICDAS dental examinations and parents will complete study measures at baseline and 12-months. An incentive up to $150 plus round-trip transit cards ($5.50 value) will be provided.

**Discussion:**

This study hypothesizes that the MSB Program can reduce ECC progression in a high-risk population. Sufficient incentives and a focus on establishing rapport between participants and CHWs are anticipated to mitigate recruitment and retention challenges. If successful, this study will advance the long-term goal of reducing pediatric oral health disparities by demonstrating the efficacy of an acceptable and feasible intervention that shifts attention from dental repair to behavioral risk mitigation.

*Trial registration*: Trial registration was completed on 4/13/2021 through the U.S. National Library of Medicine ClinicalTrials.gov website (Identifier: NCT04845594).

## Background

Dental caries in children under age six years is a persistent, prevalent, and consequential public health problem. More than one-in-five U.S. children ages 2–5 are affected (21.4%) and the disease is disproportionately concentrated in minority and socially disadvantaged populations [1]. Early childhood caries (ECC) has deleterious impacts on the child and family as well as elevating risk for future caries experience in both the primary and permanent dentitions [2–4]. Current treatment regimens focus on surgical repair and pharmacologic suppression [5] while also recognizing the need for preventive guidance to mitigate caries activity [6, 7].

Needed are behavioral strategies that mitigate caries risk for individual children and reduce ECC disparities among child populations. Twice-daily fluoridated toothpaste use [8–10], consumption of a low cariogenic diet, and health-promoting feeding and eating behaviors have both preventive and therapeutic values for young children’s oral health [8, 9, 11–14].

To date, the few US reports of behavioral interventions to reduce ECC have been predicated on theoretical constructs that include Social Cognitive Theory, Health Belief Model, Theory of Planned Behavior, and Self-determination Theory. [12–22]. Three of these studies included both clinical and behavioral outcomes [13, 15, 21] but none analyzed mediators or moderators to describe how or why the intervention was expected to improve ECC-related behaviors or reduce disease progression. What remains unknown are how to increase the adoption and maintenance of salutary behaviors by high-risk families or populations and the reasons why interventions work or fail to work to secure behavioral changes and reduce ECC incidence.

Approaches built on principles of motivational interviewing and chronic disease management have been suggested to promote such positive oral healthful behaviors [23, 24] with mixed results but some notable successes [25, 26].

One such therapeutic caries counseling behavioral approach to ECC prevention and suppression is the theory-based MySmileBuddy (MSB) Program developed by a multidisciplinary team at Columbia University [27]. An overview of the theoretical model underlying the MSB Program is presented in Fig. 1. Using the MySmileBuddy App to ensure scientific integrity, the MSB Program utilizes Community Health Workers (CHWs) to engage families of young children in home and community sites to educate parents, assess ECC risk factors, establish a personalized behavioral goal, develop an action plan to achieve that goal, and provide ongoing support and follow up. As public health workers who are considered trusted members of the communities they serve, CHWs provide an essential link to health and social services (e.g., housing and legal aid, food assistance, counseling and educational programs, etc.) and support enhanced individual and community capacity by increasing health-related knowledge and self-sufficiency [28]. The MSB Program seeks to both increase motivation and ability to adopt salutary behaviors by providing families with the knowledge, tools, social support, and material supplies to make positive changes, thereby addressing current gaps in knowledge about behavioral management of ECC.

**Fig. 1 Fig1:**
[figure not shown]
MySmileBuddy program theoretical model. This figure presents the theoretical model that is used to guide the MySmileBuddy Program intervention and analysis of causal pathways through which the intervention exerts (or fails to exert) an influence on targeted behaviors. Mediators included are drawn from MySmileBuddy’s foundation in Social Cognitive Theory and the Health Belief Model. Social Cognitive Theory is based on a wide range of motivating and facilitating determinants. This theory provides extensive guidance on translating motivation into action through its emphasis on action self-efficacy and facilitating determinants. It emphasizes that individuals and their environments mutually influence each other, and so the environment must also be addressed. Health Belief Model focuses on the motivational determinants and the benefits and barriers to taking action and self-efficacy. It is useful for audiences and settings where the emphasis is on health. The included motivational determinants bolster parents’ motivation through increasing perceived threat of caries (both perceived susceptibility and seriousness) and promoting positive outcome expectations. Facilitating determinants are influenced by CHW efforts to increase parents’ ability to act on their motivation by demonstrating skills, enhancing self-efficacy to perform these skills, providing access to tooth brushes and toothpaste, and action goal setting. In addition to these psychosocial theories, three broad evidence-based targets from the Science of Behavior Change (SOBC) program relevant to understanding mechanisms to predict whether participants are successful at action goal setting, are included

The MSB Program and App were developed with support from the National Institutes of Health (NIH; UL1TR001873, RC1MD004257), evaluated for validity of its risk components [29, 30], assessed for feasibility and acceptability when delivered to a low-income primarily Hispanic population [30–32], and tested through a pragmatic effectiveness trial with families of 1,207 children supported by the federal Center for Medicare and Medicaid Innovation (C1CMS331347). Needed to assess the Program is a randomized controlled trial (RCT) that tests the efficacy of the MSB Program in a high-risk minority population and advances understanding of its mechanisms of action. This report describes the protocol for such an RCT as developed and initiated with support from the NIH National Institute of Dental and Craniofacial Research (R34DE023158, U01DE026739). This RCT was halted in March 2020 by the COVID-19 pandemic just as recruitment began. Since that time, a grant from the Cabrini Foundation of New York City has been secured to refashion the MSB Program for virtual telehealth visits. When and if resumed, this RCT will measure factors shown to influence motivation (perceived threat, ECC contextual knowledge, and positive outcome expectations) and ability to act on motivation (knowledge and skills, self-efficacy, action goal setting, and access to toothbrushes and toothpaste) to initiate and maintain positive oral health behaviors.

## Methods/design

### Aims

The overarching aim of this prospective, single-blinded, RCT is to evaluate the efficacy of the MSB Program – a theory-based, behaviorally focused family-centered intervention – to reduce the incidence of ECC progression in a high-risk population of young children with clinically evident caries. Objectives to fulfill this aim are:

### Impact objective (primary)

To assess the MSB Program’s efficacy versus Control to decrease ECC progression, defined as positive change in number of decayed, missing, or filled teeth (∆dmft > 0) measured 12-months post-randomization. We hypothesize that the MSB Program will decrease ECC progression in Intervention Group participants at 12-months post-randomization.

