### Statistical power and data analysis

With power ≥ 80% and 2-tailed alpha = 0.05, a sample size of 300 parent–child dyads per Group is sufficient under various scenarios to detect differences between Control and Intervention Groups (45% vs. 33%, 55% vs. 43%, 65% vs. 53% or 75% vs. 64%) based on a 63.2% one-year caries progression rate among 2–5 year old children treated at the Columbia pediatric dental clinic – a rate consistent with findings from this and other high-risk populations [11, 30, 36, 37]. Accounting for 30% loss to follow up (an estimate higher than experienced in our earlier study), each group will require enrollment of 429 subjects.

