### Comparisons

Logistic regression analysis will compare the odds of having ECC progression between the Intervention and Control Group. The analysis incorporates age and recruitment site to reflect randomization on these variables. If there are any significant Group differences in participant characteristics at baseline, a sensitivity analysis adjusting for potential confounder variables in the regression models will be conducted to help interpret the primary analysis finding. To compare the increase in number of dmft/dfs, we will use a repeated measurements analytic approach.

To model the observed count data, we will use a Poisson mixed model (38, Ch.9) that introduces the number of dmft/dfs and considers these counts to be Poisson distributed conditional upon Gaussian random effects. The model includes indicators for time, Group, recruitment site, age, and Group-by-time. The regression coefficient corresponding to the interaction term is the key parameter of interest for assessing the efficacy of the MSB Program as it represents the post- to pre-treatment ratio of the average rate of dmft/dfs between the Intervention and Control Groups. A random effect is included to account for within-subject correlation and for the possibility of heterogeneity among subjects in the ratio of expected dmft/dfs counts before and after randomization. R packages will be used to fit and carry out inference for the proposed models.

Mediation analysis will be used to test of joint significance of the two paths involving a potential mediator, which was found to achieve the best balance of Type I error and statistical power across the 14 reviewed methods [39]. Potential mediators are risk perception for ECC, self-efficacy for tooth-brushing, skills for tooth brushing, self-efficacy for eating a low cariogenic diet, skills for eating a low cariogenic diet, goal setting reflecting self-regulation processes, physical environmental support, social environmental support, knowledge, positive outcome expectations, and ability to overcome barriers to tooth brushing and adoption of a low-cariogenic diet. This allows for expected partial rather than total mediation, a variable will be declared a mediator if and only if both the test of the regression coefficient of the explanatory factor on the mediator *and* the test of the coefficient of the mediator on the outcome variable are both significant at level alpha = 0.05, two-tailed.

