Key inclusion and exclusion criteria	Ages eligible for study: well-children 24–71 months of age with a minimum of 12 teeth and apparent early childhood caries (ECC) or Severe ECC (S-ECC) as defined for research purposes; parents/caregivers ≥ 18 years of age with text-capable phone planning to reside in the New York area for next 12 months
	Exclusion criteria: Children with a disqualifying medical condition (that would limit oral dietary intake, at-home oral hygiene practices, or receipt of oral examinations)
Study type	Single-blind (clinical outcomes assessor) randomized controlled trial with randomization stratified by age (24 – 48 and 49 – 71 months) and recruitment site, with approximately equal numbers in each Group using a biased-coin design facilitated by computerized randomization software
Date of first enrolment	Pending
Target sample size	858 parent/child dyads
Recruitment status	Pending
Primary outcome(s)	Change in number of decayed, missing, or filled teeth (∆dmft > 0) or surfaces (∆dfs > 0)) measured 12-months post-randomization
Key secondary outcomes	Change in twice daily therapeutic toothbrushing (twice daily with appropriate amount of fluoridated toothpaste, by parents, for at least 1 min) and consumption of a low cariogenic diet (based on recommended frequency, duration, content, and timing of cariogenic foods and drink consumption)

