## Abbreviations

**CCPH**: Columbia Community Partnership for Health
**CHW**: Community Health Worker
**DCC**: Data Coordinating Center
**dmft/dfs**: Decayed, missing or filled teeth/decayed or filled surfaces
**ECC**: Early childhood caries
**ICDAS**: International Caries Detection and Assessment System
**MSB**: MySmileBuddy
**NIDCR**: National Institutes of Dental and Craniofacial Research
**NIH**: National Institutes of Health
**RCT**: Randomized controlled trial
**S-ECC**: Severe early childhood caries
**TBOS**: Toothbrushing observation system

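### The primary outcome is an increase in affected teeth in one place and in teeth or surfaces in another, and the primary test is not clearly fixed

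*Protocol article*

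**What the plan says.** All of these statements are current text in the protocol article.

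- **Impact objective (primary):** the aim is to "decrease ECC progression, defined as positive change in number of decayed, missing, or filled teeth", written as ∆dmft > 0 at 12 months. Surfaces are not mentioned.
- **Trial registration data set, primary outcome(s):** "Change in number of decayed, missing, or filled teeth (∆dmft > 0) or surfaces (∆dfs > 0)) measured 12-months post-randomization".
- **Abbreviations:** dmft/dfs is expanded as "Decayed, missing or filled teeth/decayed or filled surfaces". The surface index therefore has no missing component.
- **Comparisons, first model:** "Logistic regression analysis will compare the odds of having ECC progression between the Intervention and Control Group", with age and recruitment site in the model. Progression is not redefined here. A sensitivity analysis adjusting for baseline imbalance is then offered "to help interpret the primary analysis finding".
- **Comparisons, second model:** a Poisson mixed model for dmft/dfs counts follows. Its Group-by-time coefficient "is the key parameter of interest for assessing the efficacy of the MSB Program".
- **Statistical power and data analysis:** one comparison of two proportions at "2-tailed alpha = 0.05", with 300 evaluable dyads per group. It refers to a 63.2% one-year progression rate without saying whether that rate counts teeth or surfaces.

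**The concern.** The two definitions can classify the same child differently:

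- A new lesion on a tooth that is already decayed or filled raises dfs and leaves dmft unchanged.
- A tooth that is sound at baseline and extracted for caries before the 12-month visit raises dmft and adds nothing to dfs.
- A decayed tooth that is extracted leaves dmft unchanged and lowers dfs.

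Such disagreements should be expected, because the Eligibility section requires confirmed caries experience at entry. Teeth already counted in dmft cannot raise it again.

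The word *or* in the registration table has two readings. One is a single composite event (teeth or surfaces progress). The other is two alternative primary outcomes. The logistic model inherits this doubt because it refers only to ECC progression. The strong wording attached to the Poisson interaction then blurs which model carries the main conclusion. At stake is whether a reader of the results can tell that the reported primary test was the one fixed in advance.

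**Working it through.** **1. The plan's own figure.** Inputs from the power section: n = 300 evaluable per group, two-sided alpha 0.05, four pairs of rates, 30% loss. The pooled-variance normal formula, with p̄ the mean of p1 and p2, is

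power = Φ{ [√n·|p1 − p2| − z·√(2p̄(1 − p̄))] / √(p1(1 − p1) + p2(1 − p2)) }, with z = 1.96.

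For 45% vs 33%: √300 × 0.12 = 2.078; 1.96 × √0.4758 = 1.352; √0.4686 = 0.6845. So (2.078 − 1.352)/0.6845 = 1.061, and power is 85.6%. The last two columns repeat the calculation at alpha 0.025 for step 4.

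| Control vs intervention | Power at 300, alpha 0.05 | n per group for 80%, alpha 0.05 | Power at 300, alpha 0.025 | n per group for 80%, alpha 0.025 |
|---|---|---|---|---|
| 45% vs 33% | 85.6% | 259 | 78.2% | 313 |
| 55% vs 43% | 83.8% | 272 | 75.9% | 329 |
| 65% vs 53% | 85.0% | 263 | 77.4% | 319 |
| 75% vs 64% | 83.5% | 274 | 75.5% | 332 |

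With a continuity correction, the n for 80% power at alpha 0.05 is 275 to 292, still within 300. Enrolment is 300/0.70 = 428.6, so 429 per group and 858 in total. The stated figures are reproduced for one binary primary outcome.

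**2. Error rate when there is one test.** If the objective governs (∆dmft > 0), or if *or* means one composite event, there is a single test and alpha is 5%. Under the composite reading the event rate cannot be lower than for dmft alone, since every dmft event is also a composite event.

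**3. Error rate if dmft and dfs were alternative primaries.** Suppose each is tested at two-sided 0.05 and either one counts as success. Then

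family-wise error = 1 − P(|Z1| < 1.96 and |Z2| < 1.96),

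with Z1 and Z2 bivariate normal with correlation ρ. At ρ = 0 this is 1 − 0.95² = 9.75%. The documents give no correlation, so the values of ρ are assumptions.

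| Assumed ρ | Family-wise error |
|---|---|
| 0 | 9.75% |
| 0.5 | 9.07% |
| 0.7 | 8.35% |
| 0.9 | 7.04% |
| 0.95 | 6.46% |

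**4. Cost of keeping both as primaries with an even split.** At 0.025 each, power at 300 per group is 75.5% to 78.2%, below the stated 80%. Restoring 80% takes 313 to 332 evaluable per group. Divided by 0.70, that is 448 to 475 enrolled per group instead of 429.

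**The case against.** The best defence is that the body of the article already points to one test. The section headed as the primary objective gives a single binary definition. The power section plans one comparison of proportions at one alpha. The Comparisons section opens with the logistic model and refers to a primary analysis in the singular before the Poisson model appears. The sentence on the interaction may mean only which coefficient of that model carries the treatment effect; the count model is nowhere called primary. A separate analysis plan may also set the order of endpoints.

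Most of this stands, and it rules out three stronger readings that a reader might infer:

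- **That alpha is not held at 5%.** No section says that dmft and dfs are each tested at 0.05 with either one sufficient. That is one reading among several, and the others give 5%.
- **That four tests (binary and count, teeth and surfaces) compete as primary.** Under an any-win rule with an assumed common correlation of 0.5 to 0.9, family-wise error would be about 15.6% to 9.3%. The article states no such rule.
- **That the sample size fits only one definition.** The scenarios cover control rates from 45% to 75%, and the 63.2% rate is not tied to either index.

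The defence does not remove the contradiction. The article states its primary outcome twice and differently. An analysis plan could choose between the statements, but one of the published statements would still be wrong.

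**Conclusion.** The point holds as an internal contradiction. The primary outcome is an increase in dmft in the objective, and an increase in dmft or dfs in the registration table. The definition used by the logistic model is not stated, and the wording on the Poisson interaction blurs a primary test that the rest of the article places with the logistic model.

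The consequence for type I error is conditional: control at 5% is not assured. The 6.5% to 9.75% range applies only if either index could win at an undivided 0.05, and it rests on assumed correlations. The sample size is sound for one binary primary, with power of 83.5% to 85.6% at 300 per group. The contradiction itself is certain from the text; the error inflation is only possible.

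**What to change.** Before enrolment resumes:

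1. State one primary endpoint and one primary test, in the same words, in the primary objective, the Comparisons section and the registration table. ∆dmft > 0 at 12 months, by the logistic model adjusted for age and recruitment site, matches the objective and the sample size. Check the registry record against this and amend it if it differs.
2. Label dfs progression and the dmft and dfs Poisson models as secondary. Reword the interaction sentence so that it identifies the treatment-effect coefficient within that model only.
3. State whether the 63.2% planning rate counts teeth or surfaces.

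The cost is wording and, if needed, a registry update, with no additional participants. The registration table still lists first enrolment as pending, so the choice can be recorded before outcome data exist. Keeping both indices as primary at 0.025 each would instead call for the larger enrolment calculated above.

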### Eligibility

Eligible parents must be 18 years or older, have a cell phone with texting capabilities, and plan to remain in the New York City metropolitan area for 12 months after enrollment (Fig. 1). Although open to all racial/ethnic groups, the demographic makeup of the targeted catchment area increases the likelihood that the majority will self-identify as Hispanic. Eligible children must be 24–71 months of age, have a minimum of 12 teeth present, have no disqualifying medical condition (that would limit oral dietary intake, at-home oral hygiene practices, or receipt of oral examinations), and have apparent ECC or Severe ECC (S-ECC) as defined for research purposes [33] on visual examination with light and dental mirror. Suspected ECC/S-ECC at recruitment will be later confirmed upon dental examination by a pediatric dentist trained in the International Caries Detection and Assessment System (ICDAS) if the child demonstrates the presence of one or more decayed (*d*) cavitated or non-cavitated lesions with ICDAS Category 2 or greater, missing (*m*) due to caries on history, or filled (*f)* tooth surfaces in any primary tooth or meets criteria for S-ECC. The ICDAS defines Category 2 as distinct visual change in enamel; Category 3 as localized enamel breakdown due to caries with no visible dentin; Category 4 as underlying dark shadow from dentin; Category 5 as distinct cavity with visible dentin; and Category 6 as extensive distinct cavity with visible dentin [34].

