### Data management

All data will be securely collected, transmitted and managed electronically in collaboration with the DCC using secure file transfer protocols and a relational database using REDCap Technology®.

Five primary sources of data will be collected about participants during the 12-month study period:*Clinical dental examination data*: Comparison of surface-level findings using ICDAS classifications at T1 and T2 will allow analyses of caries status, extent, and progression.*Tooth brushing observation data*: TBOS findings for the Intervention Group at T1 and T2 will allow analyses of changes over time while comparison of tooth brushing between Intervention and Control Groups at T2 will allow analysis of difference between toothbrushing efficacy and adherence to recommendations between the Groups.*Interview and Survey data*: Data from CHW interviews and surveys will support evaluation of participants’ sociodemographic characteristics and key motivational (e.g., perceived threat, positive outcome expectations) and facilitating (e.g., knowledge and skills, self-efficacy, action goal setting) determinants that may contribute to explaining mechanisms and putative pathways through which the MSB Program influences the study’s targeted behaviors (Fig. 2).*MySmileBuddy App data*: Data derived directly from the MSB App will describe the Intervention Group’s dietary intake, daily fluoride use, risk profiles, prevention goals, and action plans.*CHW implementation and process data*: Implementation and process data will be collected through electronic forms and logs to track date, time, duration, and disposition of each parent contact and record information on intervention tailoring and referrals for non-dental services.

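### Net ∆dmft lets a naturally shed carious tooth cancel a new lesion, and dfs has no missing component, so a caries extraction lowers it

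*Protocol article*

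**What the plan says.** The section Impact objective (primary) defines progression as a "positive change in number of decayed, missing, or filled teeth", that is ∆dmft > 0, at 12 months after randomisation. Under Comparisons, this yes/no outcome is analysed by logistic regression.

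The components of the index are described only under Eligibility. There, decay covers "cavitated or non-cavitated lesions with ICDAS Category 2 or greater", and a tooth counts as missing only when it is "missing (*m*) due to caries on history". The article gives no scoring rule for a tooth that was affected at T1 and has shed naturally by T2.

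The WHO registration table words the primary outcome more widely: "Change in number of decayed, missing, or filled teeth (∆dmft > 0) or surfaces (∆dfs > 0)) measured 12-months post-randomization". Comparisons also plans a Poisson mixed model for dmft/dfs counts. The Abbreviations list expands the pair as "Decayed, missing or filled teeth/decayed or filled surfaces", so the surface index has no missing component.

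On age, "Eligible children must be 24–71 months of age, have a minimum of 12 teeth present". On data, Enrollment describes surface-specific charting, and Data management says: "Comparison of surface-level findings using ICDAS classifications at T1 and T2 will allow analyses of caries status, extent, and progression".

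**The concern.** The stated aim is to reduce the incidence of ECC progression, but a net count measures gains minus losses. Two kinds of loss have nothing to do with better oral health.

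- **Natural shedding (dmft).** A decayed or filled primary tooth that sheds is not missing because of caries, so it drops out of dmft. One such tooth hides one newly affected tooth.
- **Extraction for caries (dfs).** The tooth's decayed or filled surfaces disappear from dfs and nothing replaces them. A bad outcome then pulls the index down, both in the ∆dfs criterion and in the Poisson model.

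The first makes the primary endpoint less sensitive to new disease. The second makes the surface index point the wrong way for the children it affects, so dmft and dfs can move in opposite directions for the same child.

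**Working it through.** **1. The plan's own figures reproduce.** Inputs from Statistical power and data analysis: two-sided alpha 0.05, 300 per group, 30% loss, and four pairs of rates. With pooled variance under the null, power = Φ{[d√n − 1.96·√(2p̄(1−p̄))] / √(p₁(1−p₁)+p₂(1−p₂))}.

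For 65% vs 53%: d = 0.12 and p̄ = 0.59, so [0.12 × 17.32 − 1.96 × 0.6956] / 0.6904 = 1.036, and power is 85.0%. The other pairs give 85.6% (45 vs 33), 83.8% (55 vs 43) and 83.5% (75 vs 64). Enrolment is 300/0.7 = 429 per group, 858 in total. The sample size is correct as calculated.

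**2. Age at T2.** Entry at up to 71 months plus 12 months gives up to 83 months. The younger stratum (24–48 months) reaches at most 60 months, so shedding concerns mainly the 49–71 month stratum.

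**3. Index arithmetic (illustrative children).**

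| Child | T1 | Events | T2 | Change | Scored as |
|---|---|---|---|---|---|
| A, dmft | 4 | one carious tooth shed (−1), one new cavity (+1) | 4 | 0 | no progression |
| B, dfs | 6 | tooth with 4 decayed surfaces extracted for caries (−4), 2 new decayed surfaces (+2) | 4 | −2 | improvement |

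In child B the extracted tooth moves from decayed to missing in dmft and stays counted, so the extraction problem belongs to dfs alone.

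**4. Power if masking is equal in both arms.** The documents give no shedding rate. Assume a share m of true progressors in each arm has a net change of zero or less, so each rate becomes p(1−m). With 300 per group:

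| m | 65 vs 53 becomes | Power | n per group for 80% | Power for 75 vs 64 |
|---|---|---|---|---|
| 0 | 65.0 vs 53.0 | 85.0% | 263 | 83.5% |
| 5% | 61.8 vs 50.4 | 80.5% | 297 | 77.2% |
| 10% | 58.5 vs 47.7 | 75.6% | 334 | 70.8% |
| 20% | 52.0 vs 42.4 | 65.4% | 424 | 58.3% |

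Check for m = 10%: [0.108 × 17.32 − 1.96 × 0.7057] / 0.7016 = 0.695, which gives 75.6%.

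**The case against.** **Scoring rules may sit elsewhere.** Rules for shed teeth are often left to a full protocol or analysis plan, and surface-level comparison is already planned. That is fair for details. But the article does fix the endpoint as a net count and does fix what counts as missing, and applied as printed these two statements give the result for child A.

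**Shedding should not bias the comparison.** This stands. Shedding depends mainly on age, and randomisation is stratified by age, so it should be similar in both arms. A reader might infer a spurious benefit of the program, but that needs losses to differ by arm. Take an assumed model with a mean of 1.5 newly affected teeth per child (gamma-Poisson, shape 1.5; 64.7% with any) and equal new disease in both arms. Losses of 0.25 vs 0.5 teeth per child then give 58.3% vs 52.5%, a gap of 5.8 points, and about 30% rejection at 300 per group. Losses of 0.05 vs 0.10 give 1.3 points and about 6%. Nothing in the documents supports a doubling in one arm.

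**Reversal is not the same problem.** A reversed non-cavitated lesion would also lower the count, and reversal could differ by arm. But the ICDAS 2 threshold is stated only for confirming eligibility. The Background also credits fluoride toothpaste and diet with therapeutic as well as preventive value, so more reversal may be a genuine effect. Netting it or not is a choice of estimand.

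**Extraction does not reverse the primary objective.** A reader might infer that the worst outcomes count as improvement in the primary endpoint. They do not in dmft. If the registration table means either criterion, a child with an extraction and a newly affected tooth elsewhere is still caught by ∆dmft. Differential extraction is also weakly supported: the additional contacts with community health workers address social needs, and all screened families are offered the same dental referral.

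**The planning rate may already be net.** If the 63.2% rate was measured as a net change, part of the masking is already in the sample size. This stands as a limit on the power figures.

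**Conclusion.** The point holds as a weakness in how the endpoint is defined. It is not a sample-size error and not a demonstrated bias between arms.

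- **dmft:** a naturally shed carious or filled tooth can hide a new lesion, mainly in the older stratum. The expected harm is misclassification and lost power. For 65% vs 53%, masking 5% leaves power just above 80%; masking 10% takes it to 75.6%, below the planned 80%. For 75% vs 64%, 5% is already enough (77.2%). The masking shares are assumptions, and the true share could be lower than all of them.
- **dfs:** extraction of a carious tooth lowers the index. This follows from the printed definition without any assumed rate, although how often it happens is not given. It affects the ∆dfs criterion in the registration table and the Poisson model for dfs, not dmft.

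The correction is worth making because it is cheap and because the registration table lists enrolment as pending.

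**What to change.** 1. Derive progression from the tooth- and surface-level charts at T1 and T2. Leave teeth shed naturally between the visits out of both counts, or carry their T1 status forward. Either way a shed tooth contributes zero to the change.
2. Replace dfs with dmfs, counting the surfaces of teeth extracted for caries, in the registered outcome and in the Poisson model.
3. State the ICDAS threshold for decay in the outcome, separately from the eligibility threshold.
4. Report incidence of any new lesion, and reversals, separately as a sensitivity analysis. Ignoring all reversals in the primary endpoint is not needed. Counting every sound-to-affected transition without netting would also turn false-positive readings by either examiner into progression.

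**Cost:** a small amount of derivation work and wording, with no new visits, participants or examinations. The charts must record why a tooth is absent at T2, which the existing definition of missing already requires. The progression rate under the revised rule may differ slightly from 63.2%, so the planning rate should be checked against the same rule where the clinic data allow.
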